An increasing number of studies have demonstrated that splenic-derived inflammatory cells are an important source of inflammatory infiltration within brain tissue and that post-stroke activation of splenic inflammatory cells invade brain tissue, exacerbating the inflammatory and thus ischemia/reperfusion(I/R) injury (4–7). It was reported that splenic contraction occurs in some stroke patients within 24–48 h, followed by gradual recovery of splenic volume with clinical function improvement, according to clinical studies (8). Animal experiments further confirmed a significant reduction in spleen volume during the acute phase of stroke and the transit of splenocytes from the spleen to the ischemic area in the brain (8, 9). These studies suggested that activation and release of splenic inflammatory cells were the key factor in exacerbating cerebral ischemia/reperfusion injury. Inhibition of the reaction may block the inflammatory cascade response in the brain, leading to neuroprotection. Because of the detrimental effects of splenic inflammatory cells and factors, splenectomy is a widely studied means of splenic suppression. Splenectomy in a mouse model resulted in lower blood levels of multiple inflammatory factors than normal mice (9), reducing inflammatory cell infiltration in the brain and reducing brain infarct volume (10). Splenic pulse treatment suppressed the immune response in septic rats (11), and splenic irradiation similarly reduced infarct volume in mice (12). However, these approaches are largely prohibited in clinical practice since they cause irreversible suppression of the spleen (10, 13, 14). In the current study, the RAH above the spleen is hypothesized to prevent splenic contraction and reduce the release of splenic inflammatory cells and cytokines, which in turn may decrease brain infarct volume and improve long-term neurological function after stroke in humans. Furthermore, before this proposed clinical trial, our team investigated the efficacy of Remote Administration of Hypothermia (RAH) to the spleen in animal models of middle cerebral artery occlusion. During the experiment, the spleen temperature was reduced to 27°C, leading to reduced brain inflammatory response, decreased infarct volume, and improved functional prognosis (unpublished data). While our original pre-clinical animal data remains unpublished, the connection between splenic response and stroke injury, as well as protective effects, has been discussed in a recent study. In this study, it was demonstrated that diminished splenic response through inactivation or knockout of GPR55 improved neurological outcomes in a rodent model (15).

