#### Secondary outcomes (efficacy)

2.5.2

(1) Effect of RAH on Spleen: (a) spleen volume measurement: Spleen CT will be performed preoperatively, 24 h and 7 days after MT to determine the change in spleen volume. The area of each layer of the spleen will be calculated by circling the area with the Siemens CT workstation image software, and the overall spleen volume will be calculated by superimposing the layer thicknesses. An ultrasound of the spleen will be performed alternatively if the CT is not done. (b) comparison of blood inflammatory profiles, the changes in inflammatory cells and inflammatory factors (including leukocytes, neutrophils, lymphocytes, tumor necrosis factor, and interleukins 6, 8, and 10, etc.) before, at 24 h and 7 days after MT will be completed. (2) Effect of RAH on Brain: (a) infarct volume (MRI-DWI) between the two groups at 7 days after MT. Infarct volume measurement of cerebral infarcts will be performed by MRI-DWI with a Siemens Syngo workstation. The area of each infarcted layer will be automatically derived by circling the region of interest (ROI) on software of the workstation, and then the overall infarct volume is calculated by superimposing the layer thickness; (b) Intracranial hemorrhage will be classified as symptomatic intracranial hemorrhage based on the following: lethal intracranial hemorrhage and symptomatic intracranial hemorrhage defined as a postoperative CT showing an intracranial hemorrhagic lesion consistent with an NIHSS deterioration score of ≥4 according to the European-Australasian Acute Stroke Study (ECASS II) criteria; (c) comparison of neurological functional independence evaluation at 90-days for functional independence ratio (mRS 0–2 score) and 90-day mortality (mRS 6 score) between RAH and control groups will be determined.

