### Estimation of sample size

2.6

This is a pilot study of the safety of RAH with MT in AIS patients with LVO of anterior circulation. There are no similar clinical studies like this, and thus, no information is available. According to Hertzog (16), 10–20 patients in each group were sufficient to assess the feasibility of a pilot study. Dobkin suggested that a minimum of 15 patients per group would be sufficient to decide whether a larger multicenter trial should be conducted (17). Therefore, we aimed to recruit 20 patients for each group in this study.

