### Statistical analyses

2.9

Data will be entered by persons not involved in the test, using double entry and setting up data range checks. Statistical analysis will be performed using SPSS version 19 (SPSS Inc., Chicago, IL, United States). Categorical variables will be expressed as percentages, and differences will be compared using the chi-square test; continuous variables conforming to normal distribution will be expressed as mean ± standard deviation, and differences will be compared using a *t*-test or ANOVA; continuous variables not all conforming to normal distribution will be expressed as median and upper and lower quartiles, and differences will be compared using rank sum test. Multi-factor linear regression or multi-factor Logistic regression analyses will be performed to control confounding factors according to the data type and outcome. *p* < 0.05 will be considered statistically significant.

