### Spleen-derived immune response and neuroprotective effects of inhibiting splenic inflammation

3.1

After a stroke, the brain and spleen communicate through various pathways, triggering immune cells to release cytokines and migrate to the affected area of the brain (25). These cytokines increase in the bloodstream around 24 h after the onset of ischemia. Levels of TNF-α, TNF-γ, IL-6, MCP-1, and IL-2 were significantly increased at 6 and 22 h after MCAO in mice with stroke injuries (26, 27). Besides, chemokines CCL2 and CCL3 attract monocytes and neutrophils after a stroke, with CCL2 peaking 2 days (28–30). Suppressing the splenic immune response after a stroke may be neuroprotective. Diminished splenic response by inactivation or knockout of GPR55 has been shown in rat models to improve neurological outcomes (15). Gu et. Al reveals external rat cooling to 30C with ETOH topically can result in neuroprotection and inhibit splenic contraction (31). Vagal nerve stimulation of the spleen has also been shown to reduce splenic inflammatory response (32).

Previous studies demonstrated that splenectomy prior to or immediately after a stroke significantly reduces infarct volume and inflammatory cell infiltration post-reperfusion in the MCAO model (10). Additionally, splenic pulsed therapy was found to suppress the immune response (11), non-surgical irradiation of the spleen in rats after MCAO reduced infarct volume (12) and inhibition a subpopulation of spleen-derived pro-inflammatory macrophages in mice resulted in a significant reduction in brain infarct volume (33).

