## Conclusion

4

This proposal attempts to confirm the safety and preliminary efficacy of RAH over the spleen and brain after stroke. The results are expected to demonstrate that RAH is safe for clinical use and has a neuroprotective effect by reversibly inhibiting splenic inflammation. This will provide a novel neuroprotective strategy. Preliminary findings will be used to set parameters for future clinical studies.

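### The inflammatory secondary outcome is an open, unranked marker list judged at p<0.05, so a chance result that could be read as mechanism is far more probable than 5%

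*Protocol article*

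**What the plan says.** All references are to the protocol article.

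- **Outcome definition (section 2.5.2).** The blood inflammatory profile covers "leukocytes, neutrophils, lymphocytes, tumor necrosis factor, and interleukins 6, 8, and 10, etc", with the changes assessed "before, at 24 h and 7 days after MT will be completed". The items are introduced as examples and the list ends in 'etc.'. No marker and no time point is put ahead of the others.
- **Threshold and tests (section 2.9).** A p-value "< 0.05 will be considered statistically significant", with no distinction between outcomes. Continuous variables are compared by t-test or ANOVA; for those that are not normal, "differences will be compared using rank sum test". Regression adjustment is also mentioned.
- **Direction (section 1).** The cooling is "hypothesized to prevent splenic contraction and reduce the release of splenic inflammatory cells and cytokines"; the Abstract says much the same. No direction is given marker by marker.
- **Background on cytokines (section 3.1).** "Levels of TNF-α, TNF-γ, IL-6, MCP-1, and IL-2 were significantly increased at 6 and 22 h after MCAO" in mice. The same paragraph places the rise of cytokines in blood at around 24 h after onset of ischemia.
- **Use of the results.** Section 3.5 says the splenic effect will be inferred indirectly from CT spleen volume and blood inflammatory factors. Section 4 expects the trial to show that the treatment "has a neuroprotective effect by reversibly inhibiting splenic inflammation", and says its preliminary findings will set parameters for later studies.
- **Size (section 2.6).** "Therefore, we aimed to recruit 20 patients for each group in this study".

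**The concern.** The panel is one of the two supports for the mechanistic claim; spleen volume is the other. As defined, it has three loose ends.

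1. The set of markers is not closed, so the text would permit a marker to be added later.
2. Nothing says which marker, at which time, would count as the main evidence of a splenic effect.
3. The general direction does not settle every item. For IL-10 and for blood lymphocytes, the document does not say whether a rise or a fall would be favourable.

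With one unadjusted threshold over many readings, an isolated p<0.05 in one marker at one time could be presented as inhibited splenic inflammation and then inform the planning of a larger trial, even though a result of that kind is not unusual when nothing is happening.

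**Working it through.** **The plan's own figure.** The only sample-size figure is 20 per group, and 2 × 20 = 40 agrees with the stated total. It comes from pilot-study rules of thumb. The article gives no power or familywise error rate for the inflammatory outcome, so there is nothing further to reproduce.

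**Inputs from the article.** Seven named markers (leukocytes, neutrophils, lymphocytes, TNF, IL-6, IL-8, IL-10); two post-thrombectomy times; threshold 0.05; 20 per group.

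**Assumptions.** Two-sided tests (sidedness is not stated); one test per marker per time; pairwise correlation between 0 and 0.7 (the article gives none).

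**Step 1: number of comparisons.** 7 × 2 = 14.

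**Step 2: independent tests, no true effect.** P(at least one p<0.05) = 1 − 0.95^14 = 0.512. Expected false positives: 14 × 0.05 = 0.70. With one time point only: 1 − 0.95^7 = 0.302.

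**Step 3: correlated tests.** Two structures were tried. In the first, all 14 test statistics share one correlation ρ. In the second, markers correlate at ρ, the two times correlate at ρ, and the two multiply for different markers at different times (20,000 simulated trials, t-tests, 20 per arm).

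| ρ | One common correlation | Markers × times |
|---|---|---|
| 0 | 51% | 51% |
| 0.3 | 44% | 46% |
| 0.5 | 35% | 39% |
| 0.7 | 25% | 29% |

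The columns differ because the structures differ; they do not conflict. The range over both is 25% to 51%.

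**Step 4: only the hypothesized direction counts.** Each test then has size 0.025. Independent: 1 − 0.975^14 = 0.298. At ρ = 0.3, 0.5 and 0.7 the common-correlation structure gives 22%, 17% and 12%, and markers × times gives 24%, 20% and 14%. The range is 12% to 30%. This takes a fall as favourable for all seven markers, which the article does not say for IL-10 or lymphocytes.

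**Step 5: what 'etc.' can add.** One extra marker gives 16 tests: 1 − 0.95^16 = 0.560 if independent. Three extra give 20 tests: 1 − 0.95^20 = 0.642 if independent, or 54%, 42% and 29% at a common ρ of 0.3, 0.5 and 0.7.

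**Step 6: after closing and ranking.** One lead reading carries a 5% chance of a false positive. Two lead readings, each at 0.05, carry 1 − 0.95^2 = 0.0975 if independent and about 0.084 at ρ = 0.7, so about 8% to 10%.

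**The case against.** **A general direction exists.** A reader might infer from the loose list that any change, up or down, could be claimed as support and that the hypothesis cannot be refuted. The article does not support that. The Abstract and section 1 predict less release of inflammatory cells and cytokines, so a rise in TNF, IL-6 or neutrophils under treatment would count against it. What is missing is the direction per marker, chiefly for IL-10 and lymphocytes.

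**A chance finding is not shown to be more likely than not.** For the named markers the figure passes 50% only if all 14 tests are independent. They are not: neutrophils and lymphocytes are part of the leukocyte count, and the same patients are measured twice. The plausible figures are lower, though still several times 5%.

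**Counting every secondary outcome would mislead.** Infarct volume, symptomatic hemorrhage, functional independence and death cannot by themselves show a splenic effect, so they do not belong in this count.

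**Separate testing is inferred.** Section 2.5.2 speaks of comparing profiles, and section 2.9 also allows ANOVA and regression. Fourteen separate tests are the natural reading, not a stated plan.

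**Much may sit in documents not shown.** A multiplicity procedure for secondary outcomes and the exact assay panel are often left to the analysis plan or full protocol, and 'etc.' may abbreviate a fuller list. That stands as far as a multiplicity procedure goes, and none is demanded here. It does not remove the point that the outcome definition, as written, is open and unranked.

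**It is a pilot with safety as primary outcome.** Efficacy is called preliminary, and no marker result is made a condition for going on to a larger trial. That limits the stakes. Against it, section 4 expects the results to show a neuroprotective effect through splenic inhibition, which goes beyond exploratory language.

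**Section 3.1 is background.** It does not decide which markers are admissible, so the absence of IL-8 and IL-10 from its list is no defect.

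**Conclusion.** The point holds in limited form. The inflammatory outcome is an open, unranked list with a general but no per-marker direction, read against a single p<0.05. If each named marker is tested at both times, the chance of at least one false positive is about 25% to 51%, which is five to ten times the nominal 5%. It is about 12% to 30% if only the hypothesized direction counts. These ranges rest on assumed correlations of 0.7 down to 0, on two-sided tests and on one test per marker per time. Any marker added under 'etc.' moves them up.

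The consequence is confined to the mechanistic reading, which draws on these markers together with spleen volume. The safety outcome is not affected. It is a cheap improvement worth making before data are seen, not a flaw that undermines the pilot.

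**What to change.** In section 2.5.2:

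1. Delete 'etc.' and close the list of markers.
2. Before data are seen, name one or two lead readings with their direction. IL-6 and TNF at 24 h, with a fall relative to sham as favourable, would be a reasonable choice: both appear in section 3.1, which also places the cytokine rise at around 24 h. The article does not dictate this choice, and the investigators may prefer another, provided it is fixed in advance.
3. For IL-10 and lymphocytes, state the favourable direction or write 'no direction claimed'.
4. Report all other markers, and all day 7 readings, as exploratory estimates with confidence intervals. Draw no mechanistic claim from an isolated p<0.05.

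Two lead readings at 0.05 each still carry about an 8% to 10% chance of a false positive, so they should be described as preliminary too.

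Cost: wording only, with no new assay, visit or patient. The downside is that an isolated significant result in another marker can no longer be claimed as evidence of mechanism.

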**Figure 1 fig1:**
[figure not shown]
Flowchart of the study.

The criteria for recruitment are as follows: (1) Age of 18–80 years; (2) Patients with AIS; (3) LVO of the anterior circulation confirmed by computer tomography angiography (CTA), magnetic resonance angiography (MRI), or digital subtraction angiography (DSA); (4) Baseline National Institute of Health stroke scale (NIHSS) score ≥ 6 and Alberta Stroke Program Early CT Score (ASPECTS) >5; (5) Less than 24 h from stroke onset; (6) Acute occlusion of intracranial or extracranial segments of the anterior circulation vessels (thrombolysis in cerebral infarction score [TICI] classification 0-I); and (7) Informed consent of the participant or legally authorized representative (in cases where the patient’s decision-making ability is impaired due to a stroke) will be obtained.

The criteria for exclusion are as follows: (1) Spontaneous revascularization or rapid spontaneous improvement in neurological function (NIHSS<6 points); (2) Unsuccessful revascularization with MT (TICI = 0); (3) Rapid improvement in symptoms after revascularization; (4) Cranial imaging showing infarct area exceeding one-third of the area supplied by the middle cerebral artery pre-MT; (5) Pre-stroke modified Rankin Scale (mRS) >2; (6) Blood glucose <2.7 or > 22.2 mmol/L; (7) Laboratory evidence of coagulation dysfunction (platelet count <40 × 10^9^/L, APTT >50 s, or INR >3.0); (8) Pregnancy; (9) Splenic-related hematologic disorders, hypersplenism, or suppression; (10) Hypersensitivity of the skin, such as cold urticaria; (11) Obesity of patients (BMI ≥28/waist circumference > 90 cm); (12) Abdominal injury, surgical trauma and other factors intolerance to splenic hypothermia; (13) Patients enrolled within 3 months prior to this clinical trial or already enrolled in another clinical trial; (14) Failure to obtain informed consent; and (15) Patients with Splenectomy.

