### Adjuvant neuroprotective strategy with RAH in addition to recanalization

3.4

As research progresses, the integration of neuroprotective measures with thrombolysis or thrombectomy is increasingly perceived as a pivotal step toward evolving comprehensive neuroprotective strategies for AIS (39, 40). Recent strides in MT for AIS have unveiled opportunities to effectively utilize additional neuroprotective treatments post-reperfusion (24, 41). Notable approaches include NA1 [an inhibitor of the excitotoxic post-synaptic density protein 95 (PSD-95)] (42), intra-arterial cooling infusion (37), and high-flow normobaric oxygen (NBO) (43). Drawing information from the neuroprotective influence of RAH over the spleen as observed in ischemic stroke animal models (submitted, unpublished data), our team would like to pioneer a clinically practical RAH methodology. This technique is geared toward establishing RAH’s neuroprotective effectiveness in AIS patients following endovascular recanalization. Our approach synergistically combines reperfusion and neuroprotection strategies, including recanalization therapy, hypothermia, and splenic inflammation inhibition. The goal is to mitigate I/R injuries and strengthen neurological function. We postulate that the combined regimen of RAH and MT might improve endovascular treatment outcomes more than MT alone. Such a combination could potentially enhance the functional outlook for AIS patients and diminish complications, including bleeding, disability, and mortality, especially in severe acute cerebral infarction cases. This comprehensive approach provides an optimized treatment model while also promoting healthcare efficiency and cost savings. By potentially reducing unnecessary medical costs, especially when using cost-effective methods like ice packs, it aligns with the broader goal of economical healthcare. Our method of regional cooling is not only user-friendly and effective but also versatile, hinting at its potential use in hypothermic treatments for different diseases and targeted organ therapies.

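### Day-7 infarct volume is compared without adjustment for pre-treatment infarct extent, although baseline ASPECTS is already collected: a minor, free gain in precision is left unused

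*Protocol article*

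**What the plan says.** **Endpoint.** Section 2.5.2 lists, as the first effect of RAH on the brain, "infarct volume (MRI-DWI) between the two groups at 7 days after MT". Regions are outlined slice by slice and "the overall infarct volume is calculated by superimposing the layer thickness", so the measure is the whole lesion. No pre-treatment infarct volume and no growth measure is given.

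**Contrast within the same section.** The spleen outcome has a baseline: "Spleen CT will be performed preoperatively, 24 h and 7 days after MT to determine the change in spleen volume". Blood markers are also taken before MT, at 24 h and at 7 days.

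**Entry criteria (section 2.2).** Patients may enter up to 24 h from onset. Inclusion criterion 4 requires "Baseline National Institute of Health stroke scale (NIHSS) score ≥ 6 and Alberta Stroke Program Early CT Score (ASPECTS) >5". An exclusion criterion reads "Cranial imaging showing infarct area exceeding one-third of the area supplied by the middle cerebral artery pre-MT". Some infarct before treatment is therefore expected, and its extent can differ between patients.

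**Aim and timing.** Section 3.4 says "The goal is to mitigate I/R injuries and strengthen neurological function". Under section 2.4, RAH starts before recanalization and ends 6 h after thrombectomy.

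**Analysis.** Section 2.9 compares continuous outcomes by t-test or ANOVA, or by rank sum test if they are not normally distributed. It adds linear or logistic multi-factor regression to control confounding, without naming a covariate or an outcome. Section 2.3 describes 1:1 computer-generated allocation and states no stratification. Section 2.6 sets 20 patients per group.

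**The concern.** Day-7 volume is the sum of infarct present before RAH starts and infarct that develops afterwards. Only the second part can respond to RAH. The first part adds between-patient spread to the outcome, and in a small trial it may differ between arms by chance. Both make an effect on later infarct harder to see. The pre-existing part also makes a given proportional reduction in later infarct look smaller when expressed against the total.

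A baseline measure that could absorb part of this spread, ASPECTS, is scored for every patient at entry, but the stated comparison does not use it. Infarct volume is the trial's only measure of infarct size, and section 4 says the preliminary findings will be used to set parameters for later studies. A needlessly imprecise estimate would carry forward.

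**Working it through.** **Inputs from the document.** 20 patients per arm (section 2.6); ASPECTS above 5, hence the five levels 6 to 10 (section 2.2); p < 0.05 (section 2.9, taken as two-sided). The sample size rests on pilot rules of thumb. It has no power calculation to reproduce, beyond 2 × 20 = 40.

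**Inputs that must be assumed.** The document gives no infarct-volume SD, no correlation r between pre-treatment extent and day-7 volume, and no share of the final infarct that is present before RAH. I take r from 0.3 to 0.7 on a suitably transformed scale, and shares of 25% to 75%.

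**1. Is the raw comparison biased?** No. In 20,000 simulated trials with a true effect of −0.80 SD and r = 0.7, the mean estimate was −0.80 both without adjustment and with adjustment for a continuous baseline measure. The SD of the estimate was 0.316 unadjusted and 0.229 adjusted. The difference is in precision only.

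**2. Chance imbalance.** In patient-level SD units, the between-arm difference in mean baseline extent has SD √(2/20) = 0.316.
- P(|difference| > 0.3 SD) = 2[1 − Φ(0.3/0.316)] ≈ 0.34
- P(|difference| > 0.5 SD) = 2[1 − Φ(0.5/0.316)] ≈ 0.11

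Only r times the imbalance reaches the outcome. At r = 0.5, an imbalance of 0.5 SD shifts the day-7 comparison by 0.5 × 0.5 = 0.25 SD, which is less than one standard error (0.316 SD).

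**3. Precision gained by adjustment.** With a continuous baseline measure, residual variance is multiplied by 1 − r². With baseline extent cut to five levels to mimic ASPECTS 6 to 10, simulation of 4,000 trials per scenario gave the ratios below. A repeat with five equally frequent levels agreed to within two percentage points.

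| Assumed r | 1 − r² (continuous) | Variance ratio, five levels | Reduction | Equivalent n per arm (20 / ratio) |
|---|---|---|---|---|
| 0.3 | 0.91 | 0.93 | 7% | about 22 |
| 0.5 | 0.75 | 0.79 | 21% | about 25 |
| 0.7 | 0.51 | 0.56 | 44% | about 36 |

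**4. Dilution of the relative effect.** Apparent reduction in total volume = reduction in later infarct × (1 − pre-existing share). For an illustrative 30% reduction in later infarct:
- share 25%: 0.30 × 0.75 = 22.5%
- share 50%: 0.30 × 0.50 = 15%
- share 75%: 0.30 × 0.25 = 7.5%

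The expected absolute difference between arms is not diluted, because pre-existing infarct is balanced in expectation.

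**The case against.** **Section 2.9 already foresees adjusted analysis, and covariate lists are commonly left to the analysis plan.** This stands in part. The absence of a covariate list from a condensed article is not itself a fault, and the planned regression could include ASPECTS. The point rests on what is stated: the specified comparison for a continuous outcome is unadjusted, and the regression is a general step against confounding that is not linked to this endpoint.

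**Total infarct at a fixed time is a valid randomized endpoint.** This stands. A reader might infer that the raw volume gives a biased answer, or that a baseline imbalance passes in full into the result. The document supports neither. Randomization balances pre-RAH infarct in expectation, only r times an imbalance carries through, and that variation is already in the standard error and type I error of the planned test. The 34% and 11% describe baseline imbalance, not false conclusions.

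**ASPECTS is used, and it limits the spread.** This stands. ASPECTS restricts entry, as does the one-third-territory exclusion. It would be wrong to say that it is unused; it is only not named for allocation or analysis.

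**The boundary is not reperfusion.** This stands. RAH begins before recanalization, so the right dividing line is the start of RAH.

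**Infarct volume is not the only brain outcome.** This stands. Section 2.5.2 also lists symptomatic hemorrhage on CT, 90-day functional independence and mortality.

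**The gain is assumed.** This stands. At r = 0.3 it is small. The simulation also treats the five-level score as an error-free grouping of infarct extent, so the figures may be optimistic.

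**Conclusion.** The point holds as a matter of precision and labelling. The main comparison of day-7 infarct volume is specified without adjustment for pre-treatment infarct extent, although a measure of it is collected at entry. The expected gain is a variance reduction of about 7% to 44% for correlations of 0.3 to 0.7. At r = 0.5 it is 21%, worth about 25 instead of 20 patients per arm. These figures rest on assumed correlations, and the dilution figures on assumed shares.

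The severity is minor. The endpoint is one of several secondary outcomes in a pilot whose primary outcome is adverse events (section 2.5.1), and the sample size does not depend on it. The remedy is also limited: ASPECTS is an ordinal score and cannot be subtracted from a DWI volume. Adjustment therefore sharpens the comparison of total infarct but does not turn it into a measure of infarct growth.

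**What to change.** In section 2.9, make the main infarct comparison a linear regression of day-7 DWI volume on treatment group, with baseline ASPECTS as a prespecified covariate. Choose the scale (log or cube root) in advance. Report the adjusted difference with its 95% confidence interval, and keep the unadjusted comparison as supportive. In section 2.5.2, label the raw volume as total infarct at day 7 rather than as injury prevented by RAH.

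The cost is about one sentence in each section and one degree of freedom. No new imaging, data or procedures are needed, because ASPECTS is already required for inclusion criterion 4.
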